## Methods/design

This pilot, single-centred, single-blinded, parallel group, prospective randomised controlled trial has been designed in accordance with the Standard Protocol Items: Recommendations for Interventional Trials (SPIRIT 2013) [30] and the Consolidated Standards for Reporting of Trials CONSORT guidelines [31] (Fig. 1, study flow diagram. The study will be undertaken at the Royal Melbourne Hospital ICU, which is a university-affiliated, tertiary referral, mixed medical-surgical-trauma ICU with 32-beds that has > 2500 patients admitted per year.

**Fig. 1 Fig1:**
[figure not shown]
Study flow diagram: flow diagram of patients recruited and study conduct. Abbreviations: *MV* mechanically ventilated, *LOMT* limit of medical treatment, *yo* years old, *FEED Protocol* intervention

### Study participants

Sixty patients will be recruited within 48 h of their index ICU admission. Screening commenced on 10th of August 2015 and is performed only on weekdays. Patients who meet the study criteria (Table 1.) will be eligible to participate. As all eligible patients are mechanically ventilated and unable to consent to participation, informed consent will be obtained from the person responsible as per local laws. Consent to continue in the trial will be obtained from the participant if they recover adequately and they are deemed competent. The protocol and consent process has been approved by the Royal Melbourne Hospital Human Research Ethics Committee (2015.048). The protocol is registered with Australian New Zealand Clinical Trials Registry (ANZCTR; U1111-1172-85630).

**Table 1 Tab1:** Inclusion and exclusion criteria

Inclusion	• Adults, ≥ 18 years of age • Mechanically ventilated (MV) for ≥ 48 h with no immediate plans to extubate in the next 24 h
Exclusion	• Patients who have a contraindication to enteral feeding • Limit of medical treatment order in place or imminent death • Pre-morbid disability causing inability to ambulate > 10 m independently (+/− gait aid) • Pregnancy • The treating clinician considers the intervention not in the patients best interest or too burdensome

### Baseline data collection

Baseline measurements will reflect the status of patients at or prior to randomisation. Demographic data includes admission diagnosis, comorbid illness including quantification using the Charlson Comorbidity Index [32], Katz Activities of Daily Living (ADL) index [33] (prior to the ICU admission), Acute Physiology and Chronic Health Evaluation II (APACHE II) score, and admission Sequential Organ Failure Assessment (SOFA) Score. Baseline measures, collected by the study Dietitian, include height (using ulna length [34]), weight (from bed scales), body mass index (BMI), mid upper arm circumference, nutritional status using the subjective global assessment (SGA) [35, 36], plasma albumin, highest and lowest blood glucose in the first 24 h of ICU admission, independent dietitian estimation of energy (weight-based or Schofield equation [37]) and protein requirements and the first quadriceps muscle layer thickness measure [24], see Table 3 for details of data collection.

### Randomisation and blinding

We will use a simple randomisation system to assign participants [1:1] to receive either standard care or the intervention. Allocation will be concealed using sequentially numbered opaque sealed envelopes, held by research personal not involved with the study. If the participant or the person responsible wishes to withdraw consent at any time, all study procedures will cease and the participant will receive standard ICU care as directed by the clinical team. Due to the nature of the intervention, the study is single-blinded. However, outcomes of muscle strength and physical function will be measured by an investigator blinded to the group allocation. Data analysis will be performed using a binary treatment code to maintain group allocation of blinding until the results are finalised.

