### Primary outcomes

The co-primary outcomes are mean daily protein and energy provided over the 15-day study period. The provision of protein and energy will be calculated on a daily basis and will be determined taking into account all sources; this includes nutrition therapy (enteral formula, protein supplements, and parenteral formula), dextrose, and propofol. The mean protein and energy provided will be determined, by adding the daily provision over the 15-day study period (the 14 complete calendar days). The provision of any nutrition prior to commencing the study protocol will be collected and reported but not included in the primary outcome analysis.

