### Sample size

A sample size of 60 is based on observational data [45], where daily protein intake, mean (SD), was 50.8 g (20.1 g) protein per day; therefore, 29 participants per group will provide 80% power (two-sided *α* 0.05) to detect a minimum difference of a 15-g protein between groups. While there is limited data on change in muscle mass using ultrasound, using the data from the VALIDUM study, mean (SD) QMLT of 1.3 (0.6) cm [22], a sample size of 28 participants in each group will also provide over 80% power to detect a mean difference of 0.5 cm in QMLT.

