All secondary outcomes will be regarded as exploratory and hypothesis-generating, with no multiple comparison adjustment to conventional 5% type 1 error thresholds. Group differences for change from baseline at selected time points in continuous outcome variables, including QMLT, will be compared after adjustment for initial values using analysis of covariance (ANCOVA) regression models, initially unadjusted, and subsequently adjusted as described below for other regression models. Natural logarithmic transformations may be applied to stabilise variance within these or other linear models if appropriate. The relationships between calorie deficits using both prescribed calories (25 kcal/kg) and MEE and protein adequacy and the outcome measures (QMLT change, muscle strength, diagnosis of ICUAW, and physical function at ICU discharge) will be explored using linear or logistic regression analyses, with adjustment for likely confounders and any baseline variable found to show substantial imbalance between treatment groups. Finally, a population-averaged generalised linear model using a generalised estimating equation (GEE) approach with an unstructured working correlation matrix and robust standard error estimates adjusted for clustering within individual subjects will be applied to these longitudinal data to evaluate the overall associations of the vector of (untransformed or log transformed) outcome variables with treatment group across multiple time points. Multiple imputations for missing data may be used to support conclusions from other generalised linear models constructed without imputation of missing data. Data analysis will be carried out using the Statistical Package for the Social Sciences (SPSS) (IBM® SPSS® Statistics Premium Grad Pack Version 22.0) or Stata Corporation (Stata Statistical Software: Release 15. College Station, TX: StataCorp LP; 2017).

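### A coded treatment variable cannot keep the analyst blind once intake data are analysed; the exposure is confined to the exploratory muscle, strength and function models

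*Protocol article*

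**What the plan says.** Randomisation and blinding calls the trial single-blinded, has strength and physical function measured by a blinded investigator, and adds an analyst blind: "Data analysis will be performed using a binary treatment code to maintain group allocation of blinding until the results are finalised".

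The co-primary outcomes are mean daily protein and energy provided. Under Primary outcomes, daily provision is built up from all sources: "this includes nutrition therapy (enteral formula, protein supplements, and parenteral formula), dextrose, and propofol". Standard care is prescribed 1.0 g/kg protein and the intervention 1.5 g/kg, both at 25 kcal/kg (Standard care group; Intervention group). Protein powder appears only in the intervention regimen, and under Management of fluid overload supplementation is increased only in that arm.

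Statistical analysis fixes the co-primary comparison as an unpaired t test at a two-sided 0.025 for each outcome. The secondary outcomes are declared exploratory, and their models leave some choices open. On transformation: "Natural logarithmic transformations may be applied to stabilise variance within these or other linear models if appropriate". On covariates, the regressions adjust for likely confounders and for "any baseline variable found to show substantial imbalance between treatment groups". The ANCOVA for change in QMLT is run first without further covariates and then with the same kind of adjustment.

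**The concern.** Replacing arm names with a neutral code blinds an analyst only if nothing else in the data identifies the arm. Here the primary outcome does. A table of protein by code, or any listing that separates out the supplement, shows which code is the intervention. The article describes no step that withholds intake data or orders the work so that other models are settled first. Protein adequacy and calorie deficit are themselves predictors in the secondary regressions, so the analyst needs intake data for part of that work.

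Two things are at stake. The report would claim an analyst blind that the design cannot deliver. Also, the choices still open in the muscle, strength and function models could be made by someone who knows the arms. The Discussion presents these outcomes as important for planning a larger trial, and the plan makes no multiplicity adjustment for them.

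**Working it through.** **Inputs** (Sample size, unless stated)
- Observational reference: "daily protein intake, mean (SD), was 50.8 g (20.1 g) protein per day".
- Planned difference: 15 g/day ("to detect a minimum difference of a 15-g protein between groups").
- 29 per group, 80% power, two-sided alpha 0.05.
- Allocation 1:1 (Randomisation and blinding).
- Formula composition: 40 g protein and 1000 kcal per litre in standard care; 63 g and 1250 kcal per litre in the intervention.

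**1. Reproduce the plan's figure.** n per group = 2 × (1.960 + 0.842)² × (20.1/15)² = 2 × 7.849 × 1.7956 = 28.2, rounded up to 29. Power at 29 is 81.1% by the normal approximation and 79.7% by the t distribution. The stated 29 is reproduced, so the same inputs can be used below.

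**2. How well does mean protein by code identify the arm?** Assume approximately normal arm means and the same SD in both arms. The intervention then has the higher observed mean with probability Φ(Δ / (SD × √(2/n))).
- Standard error = 20.1 × √(2/29) = 5.28 g.
- At Δ = 15 g: z = 15/5.28 = 2.84, probability 0.998.

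The true difference is unknown, so over a range of assumed values:

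| True difference (g/day) | z | Probability that the higher arm is the intervention |
|---|---|---|
| 5 | 0.95 | 0.83 |
| 7.5 | 1.42 | 0.92 |
| 10 | 1.89 | 0.97 |
| 15 | 2.84 | 0.998 |
| 20 | 3.79 | 0.9999 |

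**3. Protein relative to energy.** Prescribed protein per 1000 kcal is 1.0/25 × 1000 = 40 g in standard care and 1.5/25 × 1000 = 60 g in the intervention (63/1.25 = 50.4 g from its formula alone). These are prescribed ratios. Delivered ratios are shifted by propofol, dextrose, parenteral nutrition and formula changes.

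**4. The supplement component.** At 25 kcal/kg the intervention formula supplies 25/1250 × 63 = 1.26 g/kg protein, leaving 1.5 − 1.26 = 0.24 g/kg to come from powder. At an assumed 70 kg that is 16.8 g/day, or 2.8 boluses of 6 g (12 to 21.6 g/day for 50 to 90 kg). The standard care formula supplies 25/1000 × 40 = 1.0 g/kg with no powder. If supplement data are visible, they identify the arm whatever the difference in totals.

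**5. Which choices are still open?**
- Co-primary outcomes: test and threshold are fixed.
- QMLT and other continuous change outcomes: ANCOVA on the initial value is fixed as the first model. Log transformation and the further covariates are open.
- ICU-acquired weakness is binary, so transformation does not arise; covariates matter if an adjusted model is fitted.
- Longitudinal GEE: working correlation and robust errors are fixed; log or untransformed outcome is open.
- Multiple imputation: described only as support for models run without it.

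**The case against.** The strongest reply is that little turns on this. The co-primary tests cannot be steered, and the secondary outcomes are openly labelled exploratory. The baseline-adjusted ANCOVA is specified whatever covariates follow, imputation is supportive only, and the choice between t test and Wilcoxon belongs to the initial exploratory step. Strength and function have a blinded assessor, and QMLT images are stored for blinded analysis; neither safeguard depends on the analyst code. All of this stands, and it limits the point to transformation and further covariates in exploratory models.

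Second, the article does not show the dataset layout. Counting supplements towards daily provision does not establish that the analyst receives a supplement field. That is also right, so the supplement argument is conditional. The calculation on totals does not need such a field.

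Third, 0.998 supposes that the planned effect is real, while the Background and Discussion allow that the intervention might deliver less protein. This is fair, and it is why the range is shown; with small differences the totals are suggestive and not decisive.

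Fourth, an analysis plan that is not shown may fix the open choices in advance. If it does, the risk of steering largely disappears. The blinding sentence would still be wrong for any analysis that uses intake.

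A reader might infer that the primary result is open to bias, or that the secondary analyses as a whole are at the analyst's discretion. The documents support neither.

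**Conclusion.** The point holds in a limited form. The protocol claims an analyst blind lasting until results are final, and the design cannot provide it once intake is tabulated by code. Under the planning assumptions the arms are identified with probability about 0.998. This drops to about 0.83 at a true difference of 5 g/day, and identification is near certain at any difference if supplement data are seen. These figures rest on an SD of 20.1 g in both arms, 29 per arm and approximately normal means.

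No planned test, estimate or sample size is shown to be wrong here. What is affected is the accuracy of the blinding claim, together with the data-dependent transformation and covariate choices in the QMLT, strength, ICU-acquired weakness and physical function comparisons. It is worth changing because a simple ordering of the work would keep a real blind for those comparisons.

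**What to change.** Release the coded data in two stages.

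1. Give the analyst the baseline data and the QMLT, strength, ICU-acquired weakness and physical function outcomes, without intake, formula or supplement fields and without the feeding-protocol compliance record. Settle the transformations and covariates, run the between-arm models and archive both code and output.
2. Merge the intake data. Run the co-primary t tests as already fixed, then the calorie-deficit and protein-adequacy regressions.

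Reword the sentence in Randomisation and blinding so that analyst blinding is claimed only for the first stage, and state that analyses using intake data are effectively unblinded.

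No further patients or measurements are needed. Someone other than the analyst must hold back and later merge the intake fields; the article does not say who could do this. The fix is partial, because the intake-based regressions cannot be blinded in this way. Fixing their covariates before the merge would limit that remaining exposure.

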### Trial intervention and comparator

The intervention or standard care will be delivered following randomisation until ICU discharge; the patient no longer requires enteral tube feeding, or at the end of day 15, with the day of randomisation being day 1. Tolerance of enteral nutrition will be assessed and managed similarly for both groups, with prokinetic drugs (metoclopramide 10 mg q.i.d. and erythromycin 200 mg b.d.) administered if gastric residue volumes at any time equal or exceed 300 ml [38]. The need for parenteral nutrition will be determined by treating clinical staff that are not investigators and are not aware of group allocations.

### Standard care group

The comparator group will receive standard nutrition care [39], which includes commencing a standard commercially available 1.0 kcal/ml enteral formula (Nutrison® 1.0 kcal, Nutricia, Wuxi, China), providing 40 g protein and 1000 kcal per litre. Liquid nutrient will be commenced using our ICU nutrition protocol (Appendix), and the target rate will be set at 25 kcal/kg ideal body weight (IBW) [1]. This strategy is designed to prescribe 1.0 g/kg protein and 25 kcal/kg of energy per day, however it is anticipated participants will receive less than this due to interruptions to nutrition therapy [39]. For participants below or within the IBW range (defined as a BMI between 18.5–25 kg/m^2^ for 18–65 years and 22–27 kg/m^2^ for ≥ 65 years [40]), actual body weight will be used. For participants with BMI ≥ 32 kg/m^2^, an adjusted IBW will be used (IBW + 25% (actual weight – IBW)) [41].

### Intervention group

The intervention group will receive their nutrition care based on the FEED protocol (Fig. 2, FEED protocol). It is anticipated that this will provide 1.5 g/kg protein and 25 kcal/kg of energy per day. The enteral formula will be a 1.25 kcal/ml formula (Nutrison® Protein plus, Nutricia, Zoetermeer, The Netherlands), providing 1250 kcal and 63 g protein per litre. The target formula volume will be determined based on 25 kcal/kg IBW, and the difference between the protein provided from the enteral formula and the target protein requirement of 1.5 g/kg IBW will be calculated. This difference will be met using protein powder (Beneprotein®, Nestle Health Sciences, Switzerland), provided in 6 g protein boluses (1 scoop of powder (7 g), provides 6 g of protein) over the day. Beneprotein® is a commercially available product that contains 100% whey protein isolate. To ensure that the target volume of formula is delivered, at 16:00 each day, the ICU bedside nurse will calculate the volume of formula provided, compared to the target volume, and then adjust the feed rate to aim to deliver the remaining feed volume over the 8-h period to midnight, with a maximum feeding rate of 150 ml/h [11]. The data on compliance to the feeding protocol will be collected.

**Fig. 2 Fig2:**
[figure not shown]
FEED protocol: how nutrition will be delivered in the intervention group. Abbreviations: *kg* kilogramme, *IBW* ideal body weight, *g* gram, *ml* millilitre, *H*_*2*_*0* water

### Management of fluid overload

For both groups, if the attending intensivist wishes to reduce the volume of feed provided, the feed will be changed to Nutrison® Concentrate 2.0 kcal/ml, (Nutricia, Zoetermeer, The Netherlands) with a goal to provide 25 kcal/kg of energy. For the standard care group, this will mean they will receive comparable protein delivery to the 1.0 kcal formula. For the intervention group, the protein supplementation will be increased in an attempt to achieve 1.5 g/kg/day. These changes will be recorded.

### Management of withdrawal

Stopping criteria are provided (Table 2), and any withdrawals will be recorded. The data will be retained and reported for all withdrawals where allowed by patient consent. Any adverse events will be recorded and reported.

**Table 2 Tab2:** Criteria for withdrawal

Criteria	Measure
Feed intolerance	Tolerating < 40% of requirements via the enteral route for ≥ 3 days
Renal failure	If eGFR is < 25% and the patient is not commenced on continuous renal replacement therapy within 2 days
Severe oedema	> 5 L positive fluid balance, without alternative way to manage fluid balance and attending physician assesses the feed volume and additional protein to be impacting on the patients treatment after the above volume considerations have been implemented
Diarrhoea	≥ 500 ml per day or five bowel actions
Intensivist or attending physician request	No parameter
Participant/person responsible request to withdraw	No parameter

### Management of adverse events

It is not expected that any adverse events will occur in relation to the study protocol. However, each participant will be monitored regularly by study personnel for adverse events occurring throughout the study. If any adverse events do present the nature, severity, causality, and course of the adverse event will be recorded. Adverse events such as death, ischaemic bowel, renal failure, and diarrhoea will be recorded from the time of consent; if these events occur, this will be discussed with the attending ICU consultant to determine if they may be related to the study. Any severe adverse events related to the study will be reported to the Melbourne Health Human Research and Ethics Committee within 24 h of personnel becoming aware of it.

### Outcome measures

The data collection and the outcome measures are summarised in Fig. 3.

**Fig. 3 Fig3:**
[figure not shown]
Study events, data collection, and outcome measures. *****Baseline data includes age, gender, body mass index, admission diagnosis, Charlson Comorbidity Index, APACHE II score, SOFA Score, Katz Activities of Daily living (ADL) index, dietitian estimation of energy, and protein requirements. **Daily ICU data includes interruptions to feeding, fluid balance, feeding intolerance (gastric residual volumes), diarrhoea (> 300 ml per day), the presence of sepsis, renal failure, urea and creatinine levels, blood sugar levels and insulin dose (unit/day). Abbreviations: *FEED protocol* intervention, *ICU* intensive care unit, *QMLT* quadriceps muscle layer thickness, *SGA* subjective globe assessment, *MUAC* mid upper arm circumference, *LOS* length of stay, *MV* mechanical ventilation, *D/C* discharge

### Primary outcomes

The co-primary outcomes are mean daily protein and energy provided over the 15-day study period. The provision of protein and energy will be calculated on a daily basis and will be determined taking into account all sources; this includes nutrition therapy (enteral formula, protein supplements, and parenteral formula), dextrose, and propofol. The mean protein and energy provided will be determined, by adding the daily provision over the 15-day study period (the 14 complete calendar days). The provision of any nutrition prior to commencing the study protocol will be collected and reported but not included in the primary outcome analysis.

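### The co-primary t tests ignore dosing weight, which sets every patient's feeding target, and so give up precision that a prespecified covariate could recover

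*Protocol article*

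**What the plan says.** **Outcome.** The Primary outcomes section says "The co-primary outcomes are mean daily protein and energy provided over the 15-day study period". It describes no division by weight or target and prints no unit. The scale is clear from the Sample size section, which uses "daily protein intake, mean (SD), was 50.8 g (20.1 g) protein per day" and sizes the trial to "detect a minimum difference of a 15-g protein between groups".

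**Dosing.** Both arms are fed to multiples of a dosing weight. Energy is 25 kcal/kg in each. Protein is 1.0 g/kg by design under standard care, against a "target protein requirement of 1.5 g/kg IBW" in the intervention group. The dosing weight comes from height and weight measured at baseline, with rules for BMI range given under Standard care group.

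**Test.** The Statistical analysis section compares each co-primary outcome by a two-sample unpaired t test at two-sided 0.025. Adjustment for baseline values or imbalanced variables is described only for change-from-baseline and exploratory regression models.

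**Allocation.** Randomisation and blinding describes simple 1:1 randomisation and mentions no stratification.

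**Requirement-referenced measures.** Protein adequacy and calorie deficit (the latter against 25 kcal/kg) are secondary outcomes, and all secondary outcomes are declared exploratory.

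**The concern.** If a feeding target is proportional to dosing weight, a heavier patient is prescribed more in either arm. Part of the between-patient spread in grams and kcal then reflects body size, not the feeding protocol. The unadjusted t test leaves that part in its error term although the variable that explains it is known before randomisation.

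Two things are at stake. The first is precision in a trial of 60. The second is the estimate from the one trial that will be run: with simple randomisation, one arm may turn out heavier by chance, and the raw difference then moves with it. Energy is more exposed than protein, because the two arms share the same energy target and the expected relative contrast is smaller.

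**Working it through.** **1. The plan's own figure.** Inputs from Sample size: SD 20.1 g, difference 15 g, "two-sided *α* 0.05", 80% power.

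n per group = 2 × (1.960 + 0.842)² × (20.1/15)² = 28.2, so 29. This matches "29 participants per group will provide 80% power". The noncentral t gives 79.7% at 29 per group. The SD of 20.1 g is on the absolute scale and already contains body-size variation, so 29 is not wrong on this account.

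**2. Starting power at the planned threshold.** With 30 per arm, SD 20.1 g, difference 15 g and two-sided 0.025, the noncentral t gives 72%. At 0.05 it would be 81%; the gap comes from the threshold, which is a separate matter.

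**3. Share of variance due to weight.** The documents give no mean or SD for dosing weight. Assumption: mean 70 kg, SD 5 to 12 kg, intake = weight × delivery per kg, the two independent.

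Share = (SD of weight / 70)² ÷ (20.1/50.8)², with (20.1/50.8)² = 0.157:
- SD 5: 0.0051/0.157 = 3%
- SD 8: 0.0131/0.157 = 8%
- SD 10: 0.0204/0.157 = 13%
- SD 12: 0.0294/0.157 = 19%

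**4. Power by analysis.** 20,000 simulated trials per cell: 30 per arm, two-sided 0.025, normal delivery per kg, total SD held near 20.1 g, and a 15 g effect at 70 kg (15/70 = 0.214 g/kg). Intake is proportional to weight raised to the power shown. Ranges run over weight SD 5 to 12 kg.

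| Intake scales with | t test on grams | Grams, dosing weight as covariate | t test on g/kg |
|---|---|---|---|
| weight (power 1) | 70-72% | 73-81% | 74-83% |
| weight, power 0.5 | 71-72% | 72-74% | 71-72% |
| weight, power 0.25 | 72% | 71-72% | 65-71% |

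The covariate gains when weight matters and loses at most about one percentage point when it does not. Dividing by weight gains slightly more under strict proportionality but loses up to about seven points when the relation is weak.

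**5. Validity.** With no treatment effect, the gram-scale t test rejects in about 0.023 to 0.027 of simulated trials, and the mean estimated difference is about 0.

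**6. Chance imbalance in the realised trial.** SD of the difference in mean weight = SD × √(2/30). At SD 10 this is 2.58 kg, with a 95% range of ±1.96 × 2.58 = ±5.1 kg.
- Protein: 5.1 × 50.8/70 = ±3.7 g, against 15 g.
- Energy: 5.1/70 = ±7%. Over SD 5 to 12 it is ±4% to ±9%. The cluster trial cited in the Background reported a 12% increase in calories. The planned protein difference is 15/50.8 = 30% of the mean.

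**The case against.** The strongest reply is that nothing here is an error. The stated aim is a greater amount of protein and energy, the background evidence is largely in grams and kcal, and the planning figures are in grams. A gram-scale outcome answers the question asked. That stands, and is why the outcome itself should stay.

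A reader might infer that the primary comparison is biased. The documents do not support this. Randomisation makes the gram difference unbiased over repeated trials, and the type I error is kept. The ±3.7 g is not extra error on top of the test: it lies within the ordinary 95% sampling range of 1.96 × 20.1 × √(2/30) = ±10.2 g, of whose variance it is (3.7/10.2)² = 13%.

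A reader might also infer that nothing referenced to body size is reported for energy. Calorie deficit is, although only as an exploratory outcome.

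The size of the gain rests on assumptions. Dosing weight is compressed by the IBW rules, so its spread may be at the low end. Delivered amounts per kg may fall with weight, because the intervention arm's catch-up rate has a fixed ceiling and intake includes dextrose, propofol and parenteral formula. Both points stand, and both argue for a covariate over a ratio. For energy the plan states no planning SD, so the gain in power cannot be sized.

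Finally, covariate models are often left to a statistical analysis plan. Here, however, the article itself names the unadjusted t test as the primary comparison.

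**Conclusion.** The point holds as a matter of efficiency and of conditional accuracy, not validity. The plan compares intakes driven by per-kg targets with a test that leaves out dosing weight, a predictor known at baseline for every patient. Under an assumed mean of 70 kg, SD 5 to 12 kg and proportional intake, adjusting for it raises power for 15 g from about 70-72% to about 73-81%. If the relation with weight is weak, the gain is near zero and the cost is one degree of freedom.

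It is tempting to go further and redefine the co-primary outcomes per kg, since 15 g is 0.30 g/kg at 50 kg but 0.17 g/kg at 90 kg. The documents do not support that as a free improvement. It pays only if intake is close to proportional to weight, which they do not show, and otherwise it can lose power. Nor does the point call the stated 29 per group into question.

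**What to change.** - Keep mean daily protein (g) and energy (kcal) as the co-primary outcomes.
- In Statistical analysis, replace the unpaired t test for each with ANCOVA, that is, linear regression on treatment group and dosing weight, tested at the planned two-sided 0.025. Prespecify the covariate so that adjustment does not depend on an imbalance seen in the data.
- Define dosing weight by one rule for both arms, from the baseline measurements, and do not update it.
- Report g/kg and kcal/kg of dosing weight as supportive measures, so that the result can be read against the per-kg separation the arms were designed to have.

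The cost is wording in one section, a sentence on supportive reporting, and one degree of freedom. Dosing weight has to be determined for every patient to set the feed target, and ANCOVA is already in the plan for other outcomes. No new data or patients are needed, no dose changes, and the 15 g planning difference can stay as it is.
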